## Abstract

Patients’ safety can be compromised in the transition of care between healthcare sectors. Optimal information flow across healthcare sectors and individualized medication treatment tailored to each patient is vital to prevent adverse events like drug-related problems. When medication changes are made during hospitalization, it is essential to ensure that the relevant general practitioner (GP) is included in the communication chain. This randomized controlled trial examines the effect of a Medication Coordinator who facilitates medication reviews in close collaboration with patients using *My Medication Plan*. Patients in the intervention group receive the medication review in combination with including suggested medication amendments documented in their electronic discharge letter send, which is sent to their GP. The patients randomized to the control group receive standard care by the ward staff. Seventy patients from the Endocrinology and Nephrology Unit at the Hospital Sønderjylland will be included in the intervention and control groups, respectively. The primary outcome is the proportion of potentially inappropriate medications. Secondary outcomes include patient-reported outcomes, i.e., quality of life and medication burden. Additional outcomes include the patient’s medication risk score, whether the patient is readmitted, and whether the patient has contacted the staff at the hospital unit after the hospital discharge. The framework for complex intervention is applied, because it allows flexibility and adaption in meeting patients’ needs by implementing tailored, possibly complex interventions in different healthcare settings. This project will examine a particular piece in the puzzle of the complexity of conducting a medication review and communication of suggested medication amendments to the patients, healthcare at the hospital, and the GP. Hopefully, this can contribute to a reduction in the risk of potentially inappropriate post-hospital medication usage.

**Trial registration:** The study has been registered at ClinicalTrial.gov with the registration number: NCT06383364. https://clinicaltrials.gov/study/NCT06383364.

## 1. Introduction

Patient safety can be compromised in the transition between healthcare sectors, such as admission to the hospital, discharge from the hospital, visits to outpatients’ clinics, and consultations with a general practitioner (GP) [1]. Approximately 20% of patients have experienced at least one adverse event in the transition between healthcare sectors [2]. Information flow across healthcare sectors must be optimized, and medication treatment tailored to each patient to prevent adverse events [1,3,4]. This type of research can be accommodated using the framework for complex interventions described by the Medical Research Council (MRC) [5]. Complex interventions allow flexibility and adaptation to individual patients’ needs across healthcare settings during implementation [5]. The outcomes of complex interventions are due to the overall intervention rather than one specific component [5].

Patients and relatives express needs for more information about their medication treatment when transitioning from hospital to home [6–9]. A consequence of discontinuity of medication information might be adverse events like drug-related problems or unintentional non-adherence to medication [7,10–12] with aggravation of the patient’s health and illness [11–13].

Electronic medication records can be implemented to ensure access to updated medication lists across healthcare sectors [4–16]. The electronic Shared Medication Record (SMR) is used in Denmark, and the SMR comprises all prescriptions and purchases of medication from the community pharmacies [14]. Based on the patient’s medication purchases, it is possible to assess patient’s adherence to medication. Despite the intention to ensure an accurate and updated medication list, discrepancies between electronic records and the patient’s actual medication use have been demonstrated [17–20]. Medication discrepancies can be due to patient non-adherence or changes to the medication regimen after medication purchase, including discontinuation of medication treatment, incorrect dosage and timing of the dosage, and omission of a drug [17,18]. This could result in drug-related problems posing a risk to patient safety [21].

Potentially inappropriate medications (PIMs) can be used in research to reflect the quality of older patients’ medication treatment [22,23]. PIMs constitute a risk for causing drug-related problems such as falls, hospitalizations, increased morbidity and mortality [24–31]. Screening tools such as *Screening Tool of Older Persons’ Prescriptions* (STOPP) and *Screening Tool to Alert to Right Treatment version 3* [32] and *Medication Appropriateness Index* [33] have been developed to assess if patients are at risk of drug-related problems. These tools can also be used as means to describe the quality of medication treatment, but the usefulness may be inadequate [34]. In Denmark, an addition of the *Discontinuation List 2024/2025* (*Seponeringslisten 2024/2025*) [35], *The Seven High Risk-Situation Drugs* [36] and *Medication Risk Score* (MERIS) [31] have been developed as screening tools. However, none of these screening tools has been assessed regarding the prioritization of patients most in need of clinical pharmacy interventions like medication reviews. Due to scarce resources, there is a need to identify patients who will benefit the most from receiving a medication review. The screening tools can assist healthcare professionals when prioritizing patients who could benefit from a medication review with the purpose to optimize the patients medication treatment [31,37].

Medication reviews comprise a systematical and structured process where the patient’s medication treatments are critically assessed [14,26,30]. Medication reviews aim to optimize the use of medicines and minimize drug-related problems. Positive effects have been reported on the quality of medication use and reduced hospital readmissions [38–41]. However, further information about patient-reported outcomes, such as quality of life and treatment burden, is needed [40].

Communication between healthcare professionals after transitioning between sectors is essential to ensure adherence to medication changes. In Denmark, digital platforms exist to support communication, e.g. discharge letters between sectors. However, the GPs need specific instructions about managing a patient’s medication treatment after hospital discharge [12,42]. The absence of instructions could explain why medication changes made during hospitalization sometimes are not effectuated [43]. In such instances, a Medication Coordinator could be used to coordinate the communication between healthcare sectors.

A tool, *My Medication Plan*, was developed to support communication between sectors and empower patients to gain control over their medication treatment. The development of *My Medication Plan* is described in an unpublished study [conducted by [name], [name], and [name]. The development of *My Medication Plan* involving patient and patient representatives as co-designers, for submission]. *My Medication Plan* was created involving patients and patient representatives as co-designers to accommodate the patients’ needs for information and empowerment. *My Medication Plan* combines the patients’ updated SMR with information about appointments across different healthcare settings.

This randomized controlled trial aims to examine the effect of a Medication Coordinator on the quality of medication treatment measured by PIMs among hospitalized patients who use at least five medications. The Medication Coordinator facilitates medication reviews in close collaboration with the patients by applying motivational interview concepts in combination with *My Medication Plan*. The primary objective is determining the proportion of potentially inappropriate medication after hospital discharge. Secondary objectives include synthesizing data on patient-reported outcomes on quality of life and treatment burdens measured through surveys. In addition, an assessment of hospital readmission and patient contact to the ward will be included.

## 2. Methods and analysis

### 2.1. Study design

The study is a single-center randomized controlled trial assessing a complex intervention with the Medication Coordinator. The screening, enrolment, randomization to the interventions, and assessments will be conducted by MS only (Fig 1). The reporting of this protocol follows the guideline for Standard Protocol Items: Recommendation for Interventional Trials–SPIRIT 2013 [44] (S1 File). The randomized clinical trial reporting will follow the CONSORT guidelines [45].

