#### 2.1.1. Recruitment of patients

Patients will be recruited from the Endocrinology and Nephrology Unit at the Hospital Sønderjylland. The ward treats renal disease, diabetes, hormone disorders, patients with diabetic ulcers, and internal medicine patients. The ward comprises 16 beds distributed by rooms for two or four patients. Recruitment will commence in *medio* May 2024 and be completed by *ultimo* May 2025. We expect to include four patients weekly.

The inclusion criteria comprise all hospitalized patients 18 years or above, and are prescribed at least five medications specified in the Electronic Patient Journal (EPJ).

Patients are not eligible for inclusion if they are unable to communicate in Danish, are cognitively impaired, e.g. suffering from dementia or Alzheimer’s, or cannot cooperate due to, e.g. hallucination or aggressive behavior.

The Medication Coordinator will screen patients for eligibility and include relevant patients in the study. After the initial screening, the ward nurses are consulted regarding patient capability to contribute to a conversation about medication based on the patients habitual condition. The Medication Coordinator performs this task so the everyday workload of the ward staff is not increased or disturbed.

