#### 2.2.4. Medication review

The medication reviews are conducted to optimize the patients’ medication treatment. The process of optimization is through the identification of any PIMs that may be discontinued and to identify if the patients experience any drug-related problems that need to be considered. Hence, the medication review is expected to increase the quality of the patients’ medication treatment.

The definition of prescribing quality indicator used is by Lawrence and Olesen [53]: “*a measurable element of prescribing performance for which there is evidence or consensus that it can be used to assess quality*, *and hence in changing the quality of care provided* [53]”. Inspired by Wallerstedt et al [34] the measureable element of prescribing performance used to assess the quality of the patients’ medication treatment is the number of PIMs. The patients’ medications are registered according to the Anatomical Therapeutic Chemical (ATC) Classification System at level 5 [54]. The medication list is assessed for PIMs by applying: two national screening tools *(Discontinuation List 2024/2025* [35] and *the Seven High-risk Situation Medications* [36], and two international screening tools (STOPP [55] and MERIS [31,37].

The medication reviews are conducted as published by Graabæk et al. [56] but with an addition of a sixth, seventh and eight step to the existing five steps.

The patients are presented with the changes made to the medication treatment in the sixth step. The patients are encouraged to write down any important information in *My Medication Plan*. The suggested medication amendments are not implemented prior to hospital discharge, because these changes may require that the patient has been stabilized. Step 7 includes specific instructions about medication amendments in the electronic discharge summary forwarded to the GP.

As the eight step is a follow-up phone call to the patient approximately seven days after discharge. The follow-up conversations is based on the medication review carried out during hospitalization.

The concepts of motivational interviewing are applied during the medication review to focus on the patients’ needs and wishes [50,51,57,58].

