#### 2.3.3. Secondary outcome

The secondary outcomes are patient-reported outcomes about quality of life and treatment burden after 3 months, but also patient’s readmissions, and contact to the ward after 30 days. The patient’s MERIS score is calculated to estimate if a medication review could change the MERIS score and reduce the probability of experiencing a drug-related problem.

*2*.*3*.*3*.*1*. *Patient-reported outcome*. To measure patient-reported outcomes regarding the quality of life and treatment burden, the *EuroQol-5* Domain (EQ-5D) and Multi-morbidity Treatment Burden Questionnaire (MTBQ) are used [55,57]. The questionnaires are combined with a Visual Analogue Scale (VAS) regarding quality of life and treatment burden as validation. VAS assessment of subjective phenomena will be converted to numerical data [60].

The patients will fill out EQ-5D, EQ-VAS, MTBQ, and the two VAS’s at inclusion and hospital discharge. The same questionnaires are answered three months after hospital discharge, either by e-mail or telephone, conducted by the first author.

EQ-5D contains five questions regarding five domains: mobility, self-care, usual activities, pain/discomfort, and anxiety/depression, each with five answer categories: no problems, slight problems, moderate problems, severe problems, and extreme problems. Permission to use the Danish EQ-5D version has been granted by EuroQol [61].

The EQ-VAS is a vertical VAS in which patients report their perceived quality of life from 0–100 [61]. The endpoints are labelled with “*The worst health you can imagine*” (0) and “*The best health you can imagine*” (100) [61]. These measurements are used to quantify a health outcome that reflects the patient’s perception.

An additional VAS regarding quality of life is added to validate if the VAS can be applied instead of a questionnaire. The questionnaire used for the validation is the ED-Q5.

The VAS is vertical and ranges from zero (lowest quality of life) to 100 (highest quality of life) by numbers. The question asked is: “How is you quality of life today?” The endpoints are labelled with “*The worst quality of life you can imagine*” (0) and “*The highest quality of life you can imagine*” (100).

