### 2.6. Statistics analysis

Descriptive statistics will be utilized to check for exchangeability between the two groups according to baseline variables. Non-categorical data will be presented as mean and standard deviation and analyzed using a t-test or median and inter-quartile ranges analyzed with Wilcoxon rank sum test, depending on whether the given variable follows a normal distribution. Depending on Cochran’s rule, categorical data will be presented as numbers or proportions and analyzed with either a Fisher or Chi-square test. Survival outcomes will be presented with Kaplan-Meier curves.

To assess whether interaction terms will be needed in the primary analysis, we will construct a margins plot highlighting the mean of each group at each time point (baseline, at hospital discharge, and six months after hospital discharge).

The final manuscript will report 95% confidence intervals and two-sided p-values. A p-value below 5% will be considered statistically significant.

All data will be analyzed in STATA/BE version 18 or R.

The data analyst will be blinded for group allocation during the statistical analysis.

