The effect of a medication review not only depends on the different components of the intervention itself but is also highly dependent on the patient’s subjective experience [5,47]. Thus, the complex intervention model may have several positive effects, which we will assess using secondary outcomes like patient-reported quality of life and treatment burden. Some patients might find the medication review with the Medication Coordinator effective, but for others, the information passed onto the GP in the discharge summary may be more effective. Nevertheless, all components are a part of the complex intervention.

Because the resources in the healthcare sector are scarce, prioritizing the patients most in need of a medication review is a priority [84]. A Danish study in general practices has demonstrated that patients with a MERIS score above 13 would most likely benefit from a medication review [37]. The MERIS screening tool is based on patients’ renal function, the total number of medications, and the risk of harm or interactions caused by drugs [31,37]. These factors might be just as high a risk for experiencing an adverse drug-event as age. Age has been associated with increased risk of experiencing an adverse drug-event due to changes in pharmacokinetic and pharmacodynamic [85]. This may be explained by many drugs being renal excreted, hence may need dose-adjustments. These factors might indicate a risk for experiencing an adverse drug-event similar to age, which has been associated with increased risk of experiencing an adverse drug-event. This may be explained by many drugs being excreted renally, hence may need dose-adjustments. Therefore, there is a need to adjust the dose according to renal function. Patients of all ages are included in this study as younger patients could also have a high MERIS score and benefit from the intervention.

Another strength of this study is the intention to secure the information flow in the transition from the hospital to the patient’s home. Medication changes and follow-up appointments with healthcare professionals are presented to the patient by *My Medication Plan* and to the GPs via the electronic discharge summary.

A strength of the data generation process is that one person collects it. It can also be a limitation of the study as there is a risk of the Pygmalion Effect [86]. It is a limitation that the first author is performing the complex intervention.

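### The person who delivers the intervention also makes the outcome assessments, and no masked assessment is described for PIM flagging or the three-month questionnaires

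*Protocol article*

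**What the plan says.** Section 2.1 (Study design): "The screening, enrolment, randomization to the interventions, and assessments will be conducted by" a single named person only.

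Section 2.1.1 (Recruitment): "The Medication Coordinator will screen patients for eligibility and include relevant patients in the study".

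Section 2.3.3.1 (Patient-reported outcome): the follow-up questionnaires are answered "three months after hospital discharge, either by e-mail or telephone, conducted by the first author".

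Discussion: "A strength of the data generation process is that one person collects it". The same paragraph then names the Pygmalion effect as a risk and adds: "It is a limitation that the first author is performing the complex intervention".

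On the primary outcome, section 2.2.4 gives the medication review the task of identifying PIMs that might be stopped. Section 2.3.2 counts a drug as a PIM when any one of four tools flags it. Medications are "registered according to the Anatomical Therapeutic Chemical (ATC) Classification System at level 5" (section 2.2.4), and section 2.7 says the medication lists are held in REDCap.

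On masking, section 2.5 blinds the Medication Coordinator to block size, and section 2.6 says: "The data analyst will be blinded for group allocation during the statistical analysis". No other masking is described.

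**The concern.** The person who advises which PIMs to stop in one arm later assesses how many PIMs remain in both arms. In the intervention arm that person has gone through each drug with the patient. For controls, section 2.2.2 describes usual care and no such review. If any judgement enters the flagging, it can differ by arm, and it then goes straight into the primary outcome.

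The questionnaires raise a separate problem. Section 2.2.3 has the coordinator build a relationship of trust with intervention patients and telephone them about seven days after discharge. Controls have neither. A three-month telephone interview by the same person invites answers meant to please, and the Discussion itself recognises that patients may tell the coordinator what they think is wanted.

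The Discussion discloses the single-person design but gives no safeguard for either outcome. Its statement that bias would run towards no difference closes the paragraph on contamination between arms. It does not cover assessor bias, which need not run that way.

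**Working it through.** **Step 1: is the assessor the person who delivers the intervention?** No single sentence says so. It follows from four places taken together.

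- Section 2.1: one person alone screens, enrols, randomizes and assesses.
- Section 2.1.1: the Medication Coordinator screens and includes patients, so the sole assessor is the coordinator.
- Discussion: the first author performs the intervention.
- Section 2.3.3.1: the first author conducts the three-month questionnaires.

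Someone who delivers the medication reviews necessarily knows who received them, so these assessments are unmasked unless a separate masked step exists. The article describes none.

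**Step 2: how much room is there for judgement in the primary outcome?** Some is removed by design. The rule is list-based with four named tools, and section 2.3.3.4 has the MERIS score calculated by software. That does not cover flagging by the other three tools. MERIS is also described there as a patient-level score that uses renal function and the number of medications as well as drug risk. Drug codes alone therefore do not supply all its inputs. How much discretion remains cannot be read from the article.

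**Step 3: illustration of size.** The plan gives no figure for misclassification, so there is none to reproduce. It also gives no usable SD. The variance of 0.5 in section 2.4 cannot be the variance of a proportion with mean 10% to 15%, because the maximum m(1 − m) is 0.10 × 0.90 = 0.09 to 0.15 × 0.85 = 0.1275. It may denote another parameter in the simulation file, which is not shown. The SD is therefore assumed, with a range.

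Inputs: n = 70 per arm and two-sided alpha 0.05 (sections 2.4 and 2.6); SD 0.08, 0.10 or 0.15 (assumed); true effect zero; coding alone shifts the arm difference by b (assumed).

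SE = SD × √(2/70) = SD × 0.169

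P(reject) = 1 − Φ(1.96 − b/SE) + Φ(−1.96 − b/SE)

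For SD 0.10 and b = 0.01: SE = 0.0169, b/SE = 0.592, and P = 1 − Φ(1.368) + Φ(−2.552) = 0.086 + 0.005 = 0.091.

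| Shift b | SD 0.08 | SD 0.10 | SD 0.15 |
|---|---|---|---|
| 0 | 5.0% | 5.0% | 5.0% |
| 1 point | 11.5% | 9.1% | 6.8% |
| 2 points | 31.6% | 21.9% | 12.4% |

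This is a normal approximation for one comparison at one time point. It is not the global beta-regression test of section 2.6.1. It shows how sensitive a trial of this size is to a small coding difference, not how large that difference will be.

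**The case against.** The best case for the plan has four parts.

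- **Disclosure.** The authors name the single collector, the Pygmalion effect, the first author's role and social desirability as limitations. In a small single-centre project this is a known trade-off. That is fair, but disclosure does not protect the outcome.
- **Inference.** Section 2.2.4 describes PIM assessment in the passive voice, the schedule figure is not shown, and an article may leave coding procedures to the full protocol. This stands in part: who codes is inferred. But section 2.1 does assign the assessments, and assigns them to one person only.
- **Limited discretion.** The PIM rule is list-based, MERIS is computed, and an e-mailed questionnaire involves no interviewer. This stands, and it narrows the exposure to residual judgement in flagging and to telephone responses.
- **Direction.** Knowing intervention patients' drugs in depth could lead the assessor to find more PIMs in that arm, which would work against the intervention. This stands, so no sign can be claimed.

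A reader might also infer three stronger things that the document does not support.

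- **That masked coding would cost no staff time.** The analyst's blinding is stated for the statistical analysis. Outcome coding is a new task, and nothing shows that drug codes suffice for all four tools.
- **That social-desirability bias affects one arm only.** The coordinator enrols both arms, and the questionnaires are conducted without distinction by arm, so the most one can say is that it is probably greater in the intervention arm.
- **That missing about 1 PIM in 12 or 13 (0.01/0.12 = 8.3%; 0.01/0.13 = 7.7%) would reproduce the six-month gap in Table 1.** The miss rate is assumed. Table 1 has the intervention arm higher (13% v 12%), so under-flagging there would not mimic that gap. The primary test is also global across time points.

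**Conclusion.** The point holds as a weakness of design that can be reduced cheaply. It is not an error in the analysis or a contradiction in the text. As written, the plan lets the person who delivers the intervention assess the primary outcome and collect the three-month patient-reported outcomes, with no masked step described. Bias in PIM flagging is possible in either direction, and its size is unknown.

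The figure of about 7% to 12% for a 1-point shift is conditional on no true effect, 70 per arm, an assumed SD of 0.15 to 0.08 and an assumed shift. It is not an estimate of the error rate in this trial. The conclusion also rests on reading sections 2.1, 2.1.1 and 2.3.3.1 and the Discussion as referring to one person, and on there being no masked coding procedure in a document that is not shown.

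**What to change.** **PIM flagging.** Fix the rules of all four tools in writing before any outcome coding, including how the patient-level MERIS score marks an individual drug. Apply them in one batch to the stored ATC level 5 lists from baseline, discharge and six months, with allocation and time point removed. Have the analyst who is already to be blinded run it. Where a criterion needs a clinical field such as renal function, extract that field in the same way in both arms.

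**Three-month questionnaires.** Send them by e-mail first in both arms, telephone only non-responders with a fixed script, and record the mode of response. Add a sensitivity analysis by mode.

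**Cost.** Some programming and analyst time, and less case-by-case judgement in flagging. No extra visits or additional assessor are needed, and sample size and power are unchanged. Bias in the telephone responses is reduced but not removed, because the caller is still the same person.
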